## 4. Details of the Procedure

### 4.1. Test Methods

Examination of the larynx and trachea will be carried out in the ultrasound room. To avoid neonate anxiety, windows will be shadowed and the ambient light will be kept low. Each time during examination, at least one parent will be able to accompany the child and make it feel comfortable. To avoid newborn anxiety, it will not be transferred to a special couch, but rather the ultrasound examination will be conducted in its crib. Prior to that, the researcher will make sure that the newborn has eaten between half and two hours before examination, and is fully calm or asleep. Right before examination, the baby will be sedated with a 30% oral glucose solution (Glux) and if a given neonate uses a pacifier, it will be removed. A small diaper roll will be placed under the newborn’s shoulder blades to ensure that the head is slightly tilted back to clearly show the structures of the neck. Each time the researcher will make sure that the newborn’s face and chest surface is parallel or nearly parallel so the test will not disturb its breathing (Figure A1). The study procedures will not affect neonatal and mother–infant care practices at the participating centers. The ultrasound examination will last up to 5 min or shorter in cases of newborn anxiety. At any time during ultrasound, the patient’s parent will have an opportunity to interrupt it without giving a reason. In such cases, the patient will be removed from the study.

The examination will be performed using a high-class ultrasound device (Philips Epiq 7G), with the eL18-4 linear probe, using water-based, bacteriostatic and hypoallergic ultrasound gel, previously warmed in the special ultrasound gel warmer to body temperature. In every possible case, the researcher will try to use the same settings, which include most of all the highest possible frequency (18 Mhz), examination depth set at 2.5 cm, ultrasonic signal gain set between 45 and 50%, dynamic range set at 55–60, focus zone range width of about 2 cm and placed on 1 cm depth. In cases in which the images obtained with respect to single patients, using these settings, prove to be of low quality, the researcher will change them to receive the best image quality and resolution.

All ultrasound data will be gathered by doctors with at least 6 years’ experience in US examinations. Every patient will receive an individual number and a three letter code (e.g., 000 XXX), that will allow the collection of anonymous data. In each case, at least six cine loops and several still images will be collected, according to the following plan. Every cine loop will have a duration of 10 s to provide for slow movement of the probe and the most advantageous visualization of the structures under examination. The researcher will exert as little pressure as possible with the ultrasound transducer in order to best visualize individual structures, so as not to disturb the patient’s comfort and not to change the anatomy of the examined structures. The first projection will show the transverse section of the medial part of the neck from the base of the tongue, through the larynx, up to the jugular notch of the sternum. This will be firstly made with a linear probe placed on the midline of the neck, with the probe angled 90 degrees to the skin and then slowly moved upward towards the tongue, and downward towards the jugular notch. During upward movement, the probe will be tilted, so that it remains at the same angle to the skin surface. This cine loop will show the general structure and position of the hyoid bone, larynx and trachea with their anatomical relationships. This image will also visualize supraglottis with preepiglottic space, as well as infrahyoid muscles on the level of hyoid bone. To obtain second and third bilateral recordings, the researcher will place the transducer parallel to each thyroid lamina angled 90 degrees to the skin and move it slowly up and down a few centimeters to show the thyroid level of the larynx. Those images (left and right sides) will show the transverse, lateral section at the level of the glottis in order to accurately visualize the laryngeal cartilages, vocal cords and structures posterior to the thyroid cartilage. Furthermore, this image will be used for the evaluation of the posterior part of the piriform recess, the interarytenoid muscles and the anatomical relationship between the larynx and esophagus. The fourth and fifth recordings will also be bilateral, obtained technically in the same way as the previous two cine loops, but only at the level of a glottis. Those images will show the transverse, lateral section applying the M-mode option, which allows for the accurate measurement of the amplitude and duration of the movement of the vocal cords. The sixth recording, also through the transverse section in the midline of the larynx, will be carried out by arranging a probe similarly to the first cine loop, but only at the glottal level. These images will document the movement and thickness of the vocal cords and the shape of the glottis while breathing. This view will also allow one to measure the thickness of the thyroid cartilage and the angle of its lamellae and to evaluate subglottic muscles. Recordings will be archived as DICOM files. After examination, the recordings will be saved to a dedicated, password-protected external drive for further processing of the images.

In every case, during further evaluation, the researcher who carried out the ultrasound examination and other researchers with at least 5 years’ experience in ultrasonography will take the following measurements using the dedicated software (Horos, Nimble Co. LLC d/b/a Purview, Annapolis, MD USA):Width of the larynx at the level of the glottis (measurement taken in the transverse plane from the external margins of the thyroid cartilage) (Figure A2);Depth of the larynx at the level of the glottis (measurement taken in the transverse view from the external margin of the thyroid cartilage to the external border of the annular cartilage) (Figure A2);Thickness of the thyroid cartilage in the midline and on both sides transversely at the level of the glottis (in the transverse plane measurement from external margins of thyroid cartilage and vertical measurement of thyroid cartilage above the anterior commissure at the level of well-visualized arytenoid cartilages in the transverse plane) (Figure A3);Angle formed by the lamina of the thyroid cartilage (measurement taken in the transverse plane with two lines drawn tangentially to the thyroid laminae) (Figure A4);Width of the glottis during calm breathing (measured in the transverse plane with lines drawn between two medial margins of arytenoid glands when they are farthest apart during breathing) (Figure A5);Angle formed by the vocal cords during calm breathing, considering the opening angle of individual chords (measurement taken in the transverse plane with a line drawn from posterior part of the anterior commissure to the medial margins of the arytenoid gland) (Figure A6);Surface area of the glottis during calm exhalation (in order to avoid distorting the result of measuring the glottal area using the outline of its visible borders, this measurement will be taken by calculating the area of a triangle, the basis of which will be the width of the glottis, and the height will be the depth of the glottis measured from the posterior part of the anterior commissure to the line drawn to measure glottis width, measurement taken in the transverse plane) (Figure A7);Thickness of the arytenoid muscle during inhalation and exhalation (measurement taken in the transverse plane in the midline from the outer surfaces of this muscle) (Figure A8);Thickness of the vocal cords in transverse projections, tangentially to the midline (measure in the transverse, lateral plane, ventral and tangentially to the arytenoid cartilages) (Figure A9);Amplitude and duration of vocal cord movement during breathing at rest (measurement taken in the transverse, lateral plane, using M-mode as the distance between two lines drawn by the movement of the outer surface of the vocal cord—lighter than the surrounding lines);Width and depth of the trachea (measurement taken in the transverse plane of the longest transverse dimension of the trachea from the external edges of the tracheal cartilages and measurement of the longest depth of the trachea from the external margin of the tracheal cartilage to the outer part of the membranous wall) (Figure A10);Width and depth of the tracheal lumen (measurement made in the transverse plane of the longest transverse dimension and longest depth of the hypoechoic area limited by the inner edges of the tracheal cartilages and membranous wall of the trachea) (Figure A11);Thickness and width of the supraglottis (measurement taken in the transverse plane of the thickest and the widest visible part of the supraglottis) (Figure A12);Thickness of the preepiglottic space (measurement taken in the transverse plane of the thickest part) (Figure A13);Thickness of the infrahyoid muscles at the level of the thyroid cartilage and hyoid bone (measurement taken in the transverse view of the thickest dimension between the outer edges of thyrohyoid and sternohyoid muscles as a group of infrahyoid muscles in the transverse plane, at the level of well-visible hyoid bone and glottis) (Figure A14).

In order to reduce the variability of the results, only measurements taken from patients who are breathing calmly will be considered. Crying, anxious or heavy breathing patients will be marked and will not be included in the measurements. These patients will not be excluded from the study to determine the percentage of patients who can be examined without compromising comfort in this population.

In addition to the data obtained from the ultrasound examination, the following patient information from the medical history will be collected: date and time of delivery, gestational age, age at the time of the study, Apgar score at the 1st, 5th and 10th minutes of life, gender, type of delivery, birth weight and length, weight on the day of the examination.

During the next stage of the study, the images acquired in the ultrasound examination will be analyzed with the use of neural networks in order to develop artificial intelligence algorithms. The method of these analyses will be determined at a later date, depending on the quality and quantity of information collected.

To date, there is no established standard technique for ultrasound examination of the larynx and trachea with respect to newborns. Furthermore, at the time of designing and commencing the study, there is no reference standard that would allow one to compare the obtained results.

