## 3. Materials and Equipment

Ultrasound examination of larynx and trachea will be performed in the Department of Neonatology and Neonatal Intensive Care at the Medical University of Warsaw and the Department of Neonatology at Ujastek Medical Center in Cracow, in 2022–2023, in a group of three-hundred randomly selected neonates, born between 32 and 42 weeks of gestation, who are stable and do not require intubation. The examination will take place in a specially prepared ultrasound room; therefore, only stable newborns who do not require intubation will be included. Prior to that, written consent will be obtained from at least one parent prior to the examination.

Inclusion criteria:Gestational age ≥32 weeks.

Exclusion criteria:Gestational age <32 weeks;Presence of significant congenital anomalies;Intubated neonate;Unstable neonate.

As recommended by WHO for similar research projects, a representative study group should include at least 200 study participants [14]. To improve the quality and reliability of the results, the number of participants for this study was set at 300. The calculated inter-observer and intra-observer concurrence (Kappa coefficient) will be calculated for all measurements.

The examination will be performed with high-class ultrasound machine (Philips Epiq 97G device, using the eL18-4 linear probe), using water-based, hypoallergic ultrasound gel (Aquasonic 100, Parker laboratories Inc., Fairfield, CT, USA), previously warmed to body temperature.

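### Removing infants whose parents interrupt the scan probably biases upward the percentage who can be examined comfortably

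*Protocol article*

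**What the plan says.** All the relevant text is in Section 4.1 (Test Methods) of the protocol article.

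- **Parental interruption.** "At any time during ultrasound, the patient’s parent will have an opportunity to interrupt it without giving a reason". The consequence follows directly: "In such cases, the patient will be removed from the study".
- **Distress during the scan.** "The ultrasound examination will last up to 5 min or shorter in cases of newborn anxiety". No removal is attached to this route. Later in the section, crying, anxious or heavily breathing infants are flagged and give no measurements, but they stay in the study. The stated purpose is "to determine the percentage of patients who can be examined without compromising comfort in this population".
- **Start of the scan.** The researcher checks that the infant "has eaten between half and two hours before examination, and is fully calm or asleep".

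Section 3 gives the planned size: "the number of participants for this study was set at 300". No expected interruption rate and no expected value for the comfort percentage appear anywhere. The percentage is not listed among the analyses in Section 4.2 or the aims in Section 5, so it is a secondary result.

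**The concern.** The authors saw that dropping distressed infants would spoil the comfort percentage, and they wrote a rule to keep them. The interruption rule undoes part of that. Take an infant who becomes anxious. If the researcher cuts the scan short, the infant stays in and can count as not comfortably examinable. If the parent stops the scan a moment earlier, the infant leaves the study. The classification then depends on who ended the scan and not on how the infant tolerated it.

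Because no reason has to be given, stops for distress cannot be separated afterwards from stops for other causes. If infants are removed without a count being kept, the analysis cannot put them back.

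What is at stake is one feasibility figure. It bears on how readily readers accept the technique as gentle, but it is not the study's main product.

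**Working it through.** **Step 1. What removal means.** Section 4.1 uses two distinct statuses for non-calm infants: left out of the measurements, and excluded from the study. It applies the first and rejects the second, in order to preserve the percentage. For interrupted scans it uses the study-level status. Read consistently, those infants leave the denominator of the percentage as well as the measurements.

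**Step 2. Inputs.** From the documents: N = 300 (Section 3). Assumed, because the documents give nothing:
- p = true share examinable in comfort: 70%, 80% or 90%
- share interrupted and removed: 2%, 5% or 10%, so k = 6, 15 or 30 infants
- q = share of the removed infants who would have been successes: 0, one half, or equal to p

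There is no figure in the protocol to reproduce.

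**Step 3. Formula.** With S = N × p successes among all infants, the percentage after removal is (S − kq)/(N − k). Subtracting S/N gives

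bias = k(p − q)/(N − k).

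The bias is upward when q is below p, zero when q = p, and would be downward if q exceeded p.

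**Step 4. All removed infants are failures (q = 0).**

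| Interrupted | p = 70% | p = 80% | p = 90% |
|---|---|---|---|
| 2% (k = 6) | 210/294 = 71.4% (+1.4) | 240/294 = 81.6% (+1.6) | 270/294 = 91.8% (+1.8) |
| 5% (k = 15) | 210/285 = 73.7% (+3.7) | 240/285 = 84.2% (+4.2) | 270/285 = 94.7% (+4.7) |
| 10% (k = 30) | 210/270 = 77.8% (+7.8) | 240/270 = 88.9% (+8.9) | 270/270 = 100.0% (+10.0) |

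**Step 5. Half of the removed infants would have succeeded (q = 0.5).**
- 2%: +0.4, +0.6 and +0.8 points for p = 70, 80 and 90%
- 5%: +1.1, +1.6 and +2.1 points; for example (240 − 7.5)/285 = 81.6%
- 10%: +2.2, +3.3 and +4.4 points; for example (240 − 15)/270 = 83.3%

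With q = p the bias is 0.0 throughout.

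**Step 6. Scale against sampling error.** The 95% half-width is 1.96 × √(p(1 − p)/300), which is 5.2, 4.5 and 3.4 points for p = 70, 80 and 90%. At 2% interruption the bias lies well inside this margin even with q = 0. At 5% with q = 0 it is about as large as the margin (4.2 against 4.5 points at p = 80%). At 10% with q = 0 it exceeds it.

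**The case against.** **The cause of the interruption is assumed.** Parents need give no reason, and nothing in the article says that distress is the usual one. The scan lasts at most 5 minutes in an infant who starts calm or asleep, so stops may be few. A scan shortened for anxiety is a separate route with no removal attached. This stands in part: direction and size cannot be proved from the text, and the claim has to be that bias is probable. Still, an interrupted scan is by definition not a completed one, and distress is a plausible reason to stop it.

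**The rule may simply be a withdrawal rule.** Interrupting a procedure and withdrawing consent to the use of data are different acts, and the text treats the first as if it were the second. Where a parent does withdraw data, the infant must leave. The number who left can still be reported.

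**The result is minor.** This stands. The percentage appears in one clause, and the reference percentiles use calmly breathing infants only, so they are untouched.

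**The detail belongs in the full protocol or analysis plan.** That would answer a complaint about an omission. Here the article fixes a removal rule that conflicts with another rule it also fixes.

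**A stronger reading that the text does not support.** Since the researcher makes sure the infant is calm or asleep before starting, a reader might infer that infants who never settle are also left out and inflate the percentage further. The article does not say that such infants are discarded, rescheduled or uncounted. Settling the infant is also part of the technique being standardised, so a percentage obtained under that technique is a legitimate target.

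**Conclusion.** The two rules in Section 4.1 need to be reconciled. Followed as written, the removal rule takes uncompleted scans out of the denominator that the later rule is meant to protect, and it probably biases the comfort percentage upward.

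The size is unknown. With 5% interruption the bias ranges from nothing (removed infants as comfortable as the rest) to about 3.7 to 4.7 points (all removed infants failures). At 2% it is at most 1.4 to 1.8 points. These figures rest on assumed interruption rates and an assumed true percentage of 70% to 90%, and on removed infants being no more comfortable than the others.

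The documents do not support saying that the percentage is certainly biased, or that the size and mobility norms are. The change is still worth making, because it is cheap and the counts may be lost if they are not logged during recruitment.

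**What to change.** Keep the parent's right to stop exactly as it is and change only how the infant is counted. Suggested wording for Section 4.1:

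> If a parent interrupts the scan, image collection ends and no measurements are taken from that infant. The infant remains in the denominator of the percentage examined in comfort and is recorded as not completed, with the reason if one is offered. If the parent withdraws consent to data use, the infant is removed, and the number so removed is reported beside the percentage.

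Report the number of interrupted scans as well, so that a reader can work out the percentage with and without them. This matters because the new count is conservative if some stops had nothing to do with comfort. It gives (S − kq)/N, which at 5% interruption with q = 0.5 is lower by 7.5/300 = 2.5 points than the share who would have been comfortable. It is, however, the correct share of infants whose scan was actually completed in comfort.

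Cost: one changed sentence, one field in the scan log, possibly one line in the consent form, and a slightly less favourable percentage. The sample size, the measurements and the reference percentiles do not change.

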### 4.2. Analysis

Statistical analysis will be conducted using R software, version 4.2.1. or later. Norms for measurements of the larynx and trachea will be defined with the following percentiles: 5th, 10th, 25th, 50th (median), 75th, 90th and 95th. Additionally, density charts will be drafted to visualize the distribution of data for each measurement. Normality of distribution will be assessed using the Shapiro–Wilk test and based on visual assessment of histograms. Differences in each measurement between subgroups (sex, Apgar score, delivery method) will be verified using t-test and ANOVA or their non-parametric equivalents, as appropriate. Correlation analysis will be conducted between measurements of the larynx and trachea and gestational age, age at the time of the study, Apgar score at the 1st, 5th and 10th minutes of life, gender, type of delivery, birth weight and length, and weight on the day of the examination. Additionally, regression analysis (univariate and multivariate) will be used to determine the relationship between the above anthropometric measurements and measurements of the larynx and trachea.

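### The glottal area carries an expiratory label but is built on a width defined at widest opening, so the item does not fix one quantity

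*Protocol article*

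**What the plan says.** The measurement list in section 4.1 (Test Methods) of the protocol article treats glottal width and glottal area as separate items.

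- **Width.** The item is headed as a calm-breathing measurement and is taken in the transverse plane with "lines drawn between two medial margins of arytenoid glands when they are farthest apart during breathing".
- **Area.** The item is headed "Surface area of the glottis during calm exhalation". To avoid tracing the visible outline, the area is calculated as a triangle, "the basis of which will be the width of the glottis, and the height will be the depth of the glottis". That depth is "measured from the posterior part of the anterior commissure to the line drawn to measure glottis width".

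No second, expiratory width is defined in the article. Another item in the same list names both respiratory phases where both are wanted: "Thickness of the arytenoid muscle during inhalation and exhalation".

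Section 4.2 (Analysis) then says what the measurements are for: "Norms for measurements of the larynx and trachea will be defined with the following percentiles: 5th, 10th, 25th, 50th (median), 75th, 90th and 95th".

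**The concern.** The heading of the area item names one respiratory phase. Its construction refers back to a line that is defined by a different rule, the widest separation over the cycle. Unless the widest opening happens to fall in exhalation, the two instructions select different frames of the recording.

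The output is a reference range. The article says that no reference standard yet exists (section 4.1) and that its examination protocol is meant to align later studies with this one (section 1). A later user who goes by the name and measures a true expiratory area could be comparing it with a maximum-opening norm, and a normal glottis could then look small. Within the study, the examining researcher and the independent second reader could each resolve the conflict differently. That would add systematic disagreement to the agreement analysis.

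**Working it through.** The plan states no figure on this point, so there is nothing to reproduce. The check has two parts: what the wording selects, and what follows from geometry.

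**1. What the wording selects**

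| Element of the area item | What the article gives | Frame it points to |
|---|---|---|
| Name | calm exhalation | an expiratory frame |
| Base | the width of the glottis, defined once | frame of widest arytenoid separation |
| Height | anterior commissure to the line drawn for that width | the same widest frame |

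Base and height agree with each other. Neither agrees with the name.

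**2. Direction and size, height unchanged**

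Let w_max be the width at widest separation, w_exh the width in exhalation, h the height, and k = w_exh / w_max. Because w_max is the maximum over the cycle, k cannot exceed 1.

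- Area as constructed: ½ × w_max × h
- Area as named: ½ × w_exh × h
- Ratio: w_max / w_exh = 1/k, which is at least 1

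The article gives no value of k, so these values are assumptions:

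| k (assumed) | 1/k | Excess over expiratory area |
|---|---|---|
| 1.0 | 1.00 | 0% |
| 0.9 | 1.11 | 11% |
| 0.8 | 1.25 | 25% |
| 0.7 | 1.43 | 43% |
| 0.6 | 1.67 | 67% |

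**3. Sensitivity to the fixed-height assumption**

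Suppose instead that cord length L is constant and only the opening angle t changes. The triangle area is then ½ × L² × sin(t), and the ratio is sin(t_max) / sin(t_exh). For example, with t_max = 60° and t_exh = 42° (70% of maximum), the ratio is 0.866 / 0.669 = 1.29, an excess of 29%. Across assumed maximum angles of 40° to 80° and expiratory angles of 50% to 90% of the maximum, the excess runs from about 4% (80° against 72°) to about 88% (40° against 20°). The direction stays upward unless the two angles sum to more than 180°.

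**4. If the width is redrawn on an expiratory frame**

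The area then matches its name and the excess is zero. However, the width of the glottis now means the maximum in one item and an expiratory value in another, and the article does not say so. If one reader follows the construction and another follows the name, their areas differ by the same factor 1/k, always in the same direction.

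**The case against.** The strongest reply is that the article never says the stored width value is carried into the area. The area is its own item with its own phase heading and its own figure (A7, against A5 for the width). One can fairly read the heading as choosing the frame, and the words width and depth as saying where the caliper lines go on it. On that reading there is no bias, only an unstated expiratory width. The two figures are not in the text at hand and might show which was meant. This stands as a possible reading, and it is why the bias is conditional. It does not remove the written conflict, because the height is expressly taken to the line already drawn for the width.

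A reader might also infer that the widest opening belongs to inspiration, so that the label is certainly wrong and the norm certainly overstated. The article does not say in which phase the opening is widest. Its text supports only equal to or larger than, and the excess is zero in any infant whose widest opening falls in exhalation.

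A third reply is that a later user who copies the published construction would measure the same quantity as the reference, and that the researchers will be trained in the measurements (section 6). Both limit the harm. Neither helps a user who relies on the name, and training on this text does not settle which frame to use.

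Finally, one might say that frame selection is detail a condensed article leaves out. The point here is not an omission: the construction is stated in full and conflicts with its own heading.

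**Conclusion.** The inconsistency is real and lies within one measurement list. Followed literally, the item produces a maximum-opening area under an expiratory name. With height unchanged, its percentile norms are then equal to or larger than those of the true expiratory area. The size cannot be derived from the article. The illustrative 0% to 67% rests wholly on assumed width ratios of 1.0 down to 0.6, and holding cord length fixed changes the figures but not the direction over the angles tried. Under the alternative reading the problem is an ambiguous definition, not a biased norm.

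The reach is narrow: the glottal-area norm and the subgroup, correlation and regression analyses that use it. Sample size and the other measurements are unaffected. It would be tempting to extend the point to the vocal-cord angle, but that item is labelled only for calm breathing and no contradiction is shown there. I rate this as moderate. It concerns one derived measurement, and the recordings are archived, so it can be corrected without re-examining any infant.

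**What to change.** Before measurement starts, choose one of two wordings and use it in the measurement instructions and in the reported norms.

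1. **Keep the construction and change the name.** Call the item maximum glottal area, taken on the frame of widest arytenoid separation. This costs wording only, but gives no expiratory norm.
2. **Keep the name and change the construction.** Define a separate expiratory width and depth, both read from the same expiratory frame of the sixth cine loop, state how that frame is chosen, and compute the area from those two values. The depth is already measured for this item, so the cost is at most one additional width reading per loop, from DICOM recordings that are already archived.

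Under either option, all readers should work to the same frame rule, so that the agreement figures compare like with like.

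### Duration of vocal cord movement is undefined and no breathing rate or cycle length is recorded, so its norm and correlations mix cord movement with breathing rate to an unknown degree

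*Protocol article*

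**What the plan says.** Section 4.1 of the protocol article (Test Methods) includes in its measurement list "Amplitude and duration of vocal cord movement during breathing at rest". The rule given for the item is "using M-mode as the distance between two lines drawn by the movement of the outer surface of the vocal cord". The source is the fourth and fifth recordings, one per side, made "applying the M-mode option, which allows for the accurate measurement of the amplitude and duration of the movement of the vocal cords". On length and storage, the same section says "Every cine loop will have a duration of 10 s" and "Recordings will be archived as DICOM files".

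Section 4.2 (Analysis) states: "Norms for measurements of the larynx and trachea will be defined with the following percentiles: 5th, 10th, 25th, 50th (median), 75th, 90th and 95th". It then plans correlations of the measurements with gestational age, age at the study, Apgar scores, sex, delivery type, birth weight and length, and current weight, followed by regressions on the anthropometric variables.

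On breathing state, Section 4.1 requires a calm or sleeping infant. Infants who cry, are anxious or breathe heavily are left out of the measurements. Section 5 names a method for assessing vocal cord mobility as an aim, so this measurement serves a stated purpose.

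**The concern.** In resting breathing the cords open and close with each breath. A time read from that movement therefore depends on two things: how long the breath lasts, and what share of it the cord spends moving. Only the second describes the cord.

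To separate them, breathing rate or cycle length has to be known. Neither appears in the measurement list, in the patient data, or among the subgroup, correlation and regression variables.

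Two consequences follow. An infant could fall outside the duration percentiles because of breathing slowly or fast rather than because the cords move unusually. And a correlation of duration with gestation, age or weight could partly be a correlation of breathing rate with those variables. No listed analysis could tell the two apart.

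The missing definition makes this worse. Readers could time a single opening, an opening and closing, or a whole cycle, and the dependence on breathing rate differs between these.

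**Working it through.** **Step 1: what the text fixes.** The article gives no figure for duration, breathing rate or the spread of either, so there is no stated number to reproduce. Side by side:

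- Measurement list (4.1): duration is named; the only rule is a distance between two lines.
- Patient data (4.1): birth, Apgar, sex, delivery, age and size variables; no breathing rate.
- Analysis (4.2): percentiles, subgroup tests, correlations and regressions; no scaling to the cycle and no breathing variable.
- Control (4.1): calm breathing, judged qualitatively, with no rate limit.

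**Step 2: a model for the size.** All inputs here are assumptions. Let RR be breaths per minute and f the fraction of the cycle in which the cord moves, independent of RR:

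duration = f × 60/RR

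With both lognormal,

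- s(RR) = ln(high/low) / (2 × 1.645), where low and high are the assumed 5th and 95th percentiles of RR;
- s(f)² = ln(1 + CV²);
- share of log-variance due to rate = s(RR)² / [s(RR)² + s(f)²].

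Example, RR 30-60 and CV of f 10%: s(RR) = ln 2 / 3.29 = 0.211, squared 0.0444; s(f)² = ln 1.01 = 0.00995; share = 0.0444 / 0.0544 = 82%.

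| Assumed RR, 5th-95th percentile | s(RR) | CV of f 5% | 10% | 20% | 30% |
|---|---|---|---|---|---|
| 30-60 per minute | 0.211 | 95% | 82% | 53% | 34% |
| 35-55 per minute | 0.137 | 88% | 65% | 32% | 18% |
| 40-50 per minute | 0.068 | 65% | 32% | 10% | 5% |

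If duration means the whole cycle, f = 1, duration equals 60/RR and the share is 100%.

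**Step 3: what scaling to the cycle would do.** Dividing by cycle length removes the RR term. The ratio of the 95th to the 5th percentile is exp(2 × 1.645 × s), with s² = s(RR)² + s(f)² before scaling and s² = s(f)² after. For CV of f 10%:

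| Assumed RR | Ratio, duration | Ratio, fraction |
|---|---|---|
| 30-60 | 2.15 | 1.39 |
| 35-55 | 1.75 | 1.39 |
| 40-50 | 1.49 | 1.39 |

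**Step 4: can the cycle be read from what is recorded?** A 10 s trace holds RR × 10/60 cycles: 5 at 30 per minute and 10 at 60 per minute. The traces are archived, so cycle length could in principle be read from them. No such step is planned.

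**The case against.** A reader might infer that the plan sets norms in absolute time and that these would largely describe how fast the infants breathed. The documents do not support that. They give no unit for duration, so absolute time is the natural reading but still an inference. And the rate share exceeds one half only when the log-scale spread of cycle length exceeds that of the movement fraction. No figure in the article bears on either.

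Other points for the plan:

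- *The infant's state is controlled.* Infants are recently fed, calm or asleep, in dim light, and given oral glucose; restless infants are not measured. This stands in part. It narrows the rates, and if they span only 40-50 per minute with CV of f 10-30% the share is 5-32%. But without a recorded rate the study could not show how narrow the range was.
- *Duration may not be proportional to cycle length.* This stands. If it means one opening or closing movement whose time hardly depends on the breath, the shares above are too high. The text does not exclude this, which is a reason to define the measure.
- *The patient data come from the medical history, where breathing rate during the scan would not be expected.* Fair. The more telling absence is from the measurement list and the analysis variables.
- *An article may leave such detail to a fuller document.* A definition or a scaling rule could be there. But the article sets out its measurements and analysis variables item by item, and an analysis plan cannot adjust for a quantity nobody reads from the trace.
- *Absolute duration at rest is a legitimate descriptive reference.* Agreed, which is why it should be kept beside the fraction.

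**Conclusion.** The point holds in a limited form. Duration of vocal cord movement is to be measured, given percentile norms and correlated with infant characteristics, but it is not defined, and no breathing rate or cycle length is measured to accompany it. The norm and the correlations therefore mix cord movement with breathing rate to an unknown, possibly dominant, degree.

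Under the proportional model, with f independent of rate, the share of log-variance due to rate runs from about 5% to 100%. Every rate and CV behind that range is an assumption, so no single value in it should be quoted as an estimate. The calm-breathing rule reduces the problem without bounding it.

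The scope is one part of one item in the measurement list. Amplitude and the size norms are untouched. It deserves action because mobility is a stated aim and the remedy uses recordings already planned.

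**What to change.** In the Section 4.1 measurement list:

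1. Define duration separately from amplitude: its start and end on the M-mode trace, its unit, and that it is averaged over the complete calm cycles in the trace.
2. Add respiratory cycle length, read from the same 10 s M-mode traces (fourth and fifth recordings).

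In Section 4.2:

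3. Report percentiles of duration as a fraction of the cycle, beside absolute duration and breathing rate.
4. Use the fraction, or duration adjusted for cycle length, in the correlations and regressions. Adjustment is the safer choice if the fraction itself turns out to vary with rate.

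The cost is a few lines of text and several extra caliper readings per trace for each reader: about 5 to 10 cycles per trace at an assumed 30-60 breaths per minute, on two sides, so about 10 to 20 cycles per infant and reader. If that is too much, a fixed smaller number of consecutive calm cycles could be specified. No new scan is needed, and archived recordings can be read the same way.
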